#### The index of independence in activities of daily living and the instrumental activities of daily living scale

ADL is an appropriate measure to monitor changes in daily self-care activities in FRDA patients (Reetz et al., 2016; Pane et al., 2018). It is an instrument to assess functional status as a measurement of the patient's ability to perform activities of daily living independently. The Index ranks adequacy of performance in the six functions of bathing, dressing, toileting, transferring, continence, and feeding. Patients are scored yes/no for independence in each of the six functions. A score of 6 indicates full function, 4 indicates moderate impairment, and 2 or less indicates severe functional impairment.

IADL is an instrument to assess independent living skills. These skills are considered more complex than the basic activities of daily living as measured by ADL. The instrument is most useful for identifying how a person is functioning at the present time, and to identify improvement or deterioration over time. Patients are scored according to their highest level of functioning in that category. A summary score ranges from 0 (low function, dependent) to 8 (high function, independent) for women, and 0 through 5 for men.

#### 9-hole pegboard test

The 9-HPT is a brief, standardized, quantitative test of upper extremity function. Both the dominant and non-dominant hands are tested twice. On a start command when a stopwatch is started, the patient picks up the nine pegs one at a time as quickly as possible, puts them in the nine holes, and, once they are in the holes, removes them again as quickly as possible one at a time, replacing them into the shallow container. The total time to complete the task is recorded. Two consecutive trials with the dominant hand are immediately followed by two consecutive trials with the non-dominant hand.

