### Study population

The trial will enroll patients from our outpatient clinic of hereditary ataxias at the AOU Federico II University. Our outpatient clinic currently follows 120 patients with molecular diagnosis of FRDA with regular bi-annual visits. An additional number of patients attend the center on a less regular basis. Patients' clinical and molecular data are stored in an electronic database that will be used for pre-screening purposes. We will enroll patients based on prescreening procedures, i.e., already known patients, through enrollment calls via the Italian association for Ataxia (AISA).

During our last phase II trial with EPO, we managed to recruit 46 patients in a 24-week interval (Saccà et al., 2016). For that study, inclusion/exclusion criteria were more stringent as patients were required to be able to perform a cardiopulmonary exercise test with an arm ergometer. We were able to include patients with a SARA score up to 32 and have them perform the CPET. Based on the inclusion/exclusion criteria of this trial, we will be able to complete enrollment during a 24-week interval.

Based on inclusion criteria, and in a similar way to the previous trial (Saccà et al., 2016), we will include patients with an age equal to or higher than 12 years. The reason for dosing minors is that FRDA does affect teenagers and children. This group is considered as a whole; exclusion of minors would lead to biased results and exclude patients who would benefit more from an innovative treatment. In addition, the use of DMF in minors does not require any additional test, nor did it raise any additional side effects as compared to adults. In the present study, it will be up to the physician's discretion to exclude patients not able to perform CPET from the trial.

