#### Secondary endpoints

The secondary clinical objectives are to examine changes on the cardiopulmonary exercise outputs (VO_2_max, anaerobic threshold, and peak workload) and echocardiographic measures; and to evaluate differences in the Scale for the Rating and assessment of Ataxia (SARA), modified Friedreich Ataxia Rating Scale (m-FARS), 9-hole pegboard test (9HPT), EQ-5D, Activities of Daily Living (ADL)/Instrumental Activities of Daily Living Scale (IADL), and number and distribution of serious and non-serious adverse events between DMF and placebo.

The secondary laboratory objectives are to determine the effect of DMF on *FXN* and frataxin protein considering the change from baseline to week 12 and week 24 and at week 1 of the core phase, and at week 1 of the extension phase for those patients transitioning from placebo to DMF, compared to other time-points obtained after a DMF dose of 240 mg BID. Other secondary endpoints explore the effect of DMF on Nrf2 pathway genes (*NFE2L2, NQO1, HMOX1, PDLIM1*, and *NCF2*), on mitochondrial biogenesis genes (mt-ND6, mtCYB, mt-CO_2_, and mt-ATP6), and on mtDNA/nDNA.

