### Statistical analysis

All data will be preliminary tested for normality using the Kolmogorov–Smirnov test. Since quantitative real time PCR (qPCR) data are frequently not normal, a normalization attempt, using ln or log transformation, will be performed. qPCR data will be calculated as relative increases imputing a baseline expression level of 1.0. Main statistical analysis of both FXN expression and frataxin protein level will be conducted with a Generalized Linear Model (GLM) for repeated measures. GLM incorporates a two-way ANOVA for repeated measures and can accommodate a multivariate analysis of factors and covariates. Treatment with DMF or placebo will be considered as a factor, and baseline levels of frataxin will be considered as a covariate. FXN baseline expression will not be used in the model as it is already integrated using relative expression with common baseline. All other available data (sex, age, disease duration, GAA1, and treatment specific findings, etc.) will be preliminarily tested one by one as covariates. In case of resulting *p*-values < 0.1, they will be integrated in the final multivariate model with treatment as a factor. In case of a significant Maulchy's sphericity test, we will use the Greenhouse-Geisser correction. We will use a similar analysis approach for remaining secondary endpoints. This will include different time-points from FXN and frataxin, and other qPCR analysis, SARA, 9HPT, PRT, ADL/IADL, and EQ-5DVAS. The main analysis will be conducted with results from the core phase of the trial (20 patients treated with DMF and 20 with placebo) and will be used to draw conclusions on the efficacy of DMF. A secondary analysis will be conducted adding to the model patients from the extension phase that switched from placebo to DMF (total of 40 DMF vs. 20 placebo). This analysis will be considered as descriptive and not used to drive efficacy conclusions. For adverse events (AEs), we will perform a descriptive analysis of AEs including their distribution in DMF and placebo treated patients, AEs duration, severity, and connection to the study drug. To test if treatment with DMF increases the likelihood of having an AE, we will use a Generalized Linear Model with Poisson distribution and treatment as a factor. To test if a single AE is more frequently linked to DMF treatment, we will use the exact test of Goodness of fit, assuming an equal proportion of adverse events in the treatment and placebo group. This will be possible only for adverse events occurring at least once in both groups. For baseline variables a descriptive analysis will be performed, and difference between DMF and placebo patients will be tested with an unpaired *t*-test and chi-square test, depending on the variable. In case of non-normal distribution, a Mann–Whitney test will be used in place of a *t*-test. A two-sided significance level of 5% will be required to reject the null hypothesis that the outcome measures are the same before and after treatment, and for all other comparisons. The Bonferroni correction for multiple analyses will be used. Considering the primary endpoint and the phase of the trial, the analysis will be per protocol. Data will be analyzed using the SPSS 23 for MAC (IBM, Chicago, USA).

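### The 9-hole pegboard test is scored as completion time and put through a repeated-measures model, so a patient who tries but cannot finish has no value and is left out

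*Protocol article*

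**What the plan says.** The protocol article names the test as a secondary clinical endpoint (Secondary endpoints: "modified Friedreich Ataxia Rating Scale (m-FARS), 9-hole pegboard test (9HPT), EQ-5D"). Its own section states that "Both the dominant and non-dominant hands are tested twice" and that "The total time to complete the task is recorded". That section gives no time limit, no value for an unfinished attempt, and no way of combining the four times from a visit.

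Under Statistical analysis, FXN expression and frataxin protein "will be conducted with a Generalized Linear Model (GLM) for repeated measures". The model is described as a two-way repeated-measures ANOVA, with a sphericity test and Greenhouse-Geisser correction, run in SPSS and per protocol. The same section adds: "We will use a similar analysis approach for remaining secondary endpoints", and lists "SARA, 9HPT, PRT, ADL/IADL, and EQ-5DVAS" among those covered. It tests all data for normality. The ln or log step is introduced for qPCR data, and the text does not say clearly whether it extends to the 9HPT.

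Table 2 schedules the 9HPT at baseline, week 12 and week 24. Table 1 has no upper limit on ataxia severity. Study population calls the criteria of the earlier trial stricter and says of it: "We were able to include patients with a SARA score up to 32 and have them perform the CPET". Physicians may exclude patients who cannot do the exercise test.

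**The concern.** Completion time is undefined for the patients with the poorest hand function. A patient who cannot place and remove nine pegs at baseline or week 12 has no time for that visit. A classical repeated-measures ANOVA needs a value at every modelled visit, so one failed visit removes the patient from the model.

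The comparison is then restricted to patients able to finish at both visits, a condition that depends partly on performance after randomisation. A patient who gains or loses the ability to finish shows a very large change on this test, and that change is discarded. If DMF improved or worsened hand function in the most severe patients, the analysis could miss it. The direction of any bias cannot be stated in advance.

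A secondary worry is efficiency. If raw times are right-skewed, slow patients contribute a disproportionate share of the variation in change.

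**Working it through.** **The plan's own figure.** The article gives no mean, SD, completion rate, target difference or power for the 9HPT, so there is no 9HPT figure to reproduce. The sample size for the primary endpoint does reproduce:

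- f = √(0.198/0.802) = 0.497.
- With two groups and two measurements, λ = f²(N − 2) = 0.497² × 34 = 8.40 at N = 36, and power is 0.804.
- 36/0.9 = 40.

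The 9HPT point does not affect this.

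**Does a non-finisher get a value?** The recorded variable is time to complete. An unfinished attempt has none. A log of a missing time is still missing, so the ln/log step would not help even if it applied here.

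**What is lost.** Assumed times for one hand:

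- A completer going from 60 s to 54 s changes speed by 1/54 − 1/60 = 0.00185 tests per second, and is kept.
- A patient going from unable to 100 s changes by 1/100 − 0 = 0.0100, which is 5.4 times as large (0.0100/0.00185), and is dropped under time scoring.

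**How many patients?** No documented rate exists.

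- If 10% to 20% fail at some visit: 0.10 × 40 = 4 to 0.20 × 40 = 8.
- If times are lognormal with median 60 s, within-patient log-SD 0.10 and failure above 180 s: 0.01, 0.7 and 2.7 of 40 at between-patient log-SD 0.3, 0.5 and 0.7.

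The span is therefore about 0 to 8, set wholly by assumption.

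**Power.** These are simulations with 20 per arm and a two-sided t-test on change, all on assumed inputs. Set A uses the lognormal inputs just given, DMF about 10% faster and 4,000 runs per setting:

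| Between-patient log-SD | 0.3 | 0.5 | 0.7 |
|---|---|---|---|
| Raw time, non-finishers dropped | 0.53 | 0.48 | 0.43 |
| Speed, non-finishers scored 0 | 0.58 | 0.51 | 0.44 |
| Log time, if everyone had a value | 0.59 | 0.60 | 0.60 |

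Speed gains 5, 3 and 1 points over raw time. Across further settings the difference ran from about −2 to +7 points.

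Set B has everyone finishing, DMF 12% faster and between-patient log-SD 0.4, 0.6 and 0.8:

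- raw time 0.68, 0.61, 0.52
- speed 0.74, 0.68, 0.56
- log time 0.78, 0.80, 0.79

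Log time is strongest in both sets.

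**Skew.** In Set A the 4 most extreme of 40 patients carry 48%, 56% and 63% of the residual sum of squares on raw seconds. This needs a benchmark. For normally distributed changes the most extreme tenth already carries about 2 × (1.645 × 0.1031 + 0.05) = 0.44, where 1.645 is the upper 5% point and 0.1031 the density there. The excess is about 4 to 19 percentage points.

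**The case against.** The strongest reply is that this is built on silence. The article does not say that non-finishers are dropped. A time cap or a could-not-complete code may sit in a rater manual, the full protocol or the SAP, and a condensed article need not repeat it. That stands as a limit: if such a rule exists, the point is already met. What remains is what the article does fix, namely a metric with no value at the severe end and a model that needs a value at each visit. For the PATA rate test it fixes a 10-second count and averages both trials, so a slow patient still scores.

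Secondly, high SARA totals need not mean unusable hands. Five of the eight items are gait, stance, sitting, speech and heel-shin, and the patients with scores up to 32 did perform an arm-ergometer test. Discretionary exclusion may also remove some severe cases. This stands in part, and non-completion may be rare. But cranking an ergometer is not a dexterity test, and the exclusion is not a 9HPT rule.

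Thirdly, seconds are an accepted way to report the test, and log time has more power than speed. Among completers that is right. It does not give a non-finisher a value.

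**Conclusion.** The point holds as a modest improvement to one secondary endpoint. Completion time in a complete-case repeated-measures model excludes patients because of their result and discards changes between unable and able. This rests on two inferences: that no scoring rule exists elsewhere, and that the model is the listwise SPSS procedure its description suggests.

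A reader might infer more than the document supports:

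- *That 4 to 8 patients will be lost.* The completion rate is undocumented, and other assumptions give fewer than one to about three.
- *That a few slow patients dominate the arm means.* No 9HPT distribution is given, normality is to be tested, and the simulated concentration is only moderately above what normal data show.
- *That speed scoring buys appreciable power.* The simulated gain over raw time is a few points at most and sometimes negative.

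The justification is retention and freedom from outcome-dependent exclusion. The primary analysis and the 36/40 sample size are unaffected.

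**What to change.** Add an eCRF tick-box, per hand and visit, for a test attempted but not completed, kept apart from a test not done. If it is not captured at the visit, failure may be impossible to separate later from a missed test.

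Add one scoring sentence: 9HPT is analysed as speed, the reciprocal of completion time, averaged over the two trials of each hand and over both hands, with 0 for a hand attempted but not completed. The sentence should also say what is entered when only one of a hand's two trials is finished. A rank-based analysis with non-completion as the worst rank would serve equally well. Tests not attempted stay missing.

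Report log time in completers as a sensitivity analysis, since it has more power in that group, and show raw seconds descriptively.

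The cost is one sentence and one eCRF field. The unit becomes tests per second (multiply by nine for pegs per second), which is less familiar than seconds, and a gain in power over raw time is not guaranteed.

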#### PATA rate test

The PRT allows for a quick screening test to assess dysarthria. Probands will be invited to repeat the syllables “PA-TA” as quickly as possible during a 10-s interval. The test will be immediately repeated for a second time. Both trials are then averaged for final score determination (Reetz et al., 2021).

#### The cardiopulmonary exercise test

CPET will be performed using an upper limb cycle ergometer (Ergoselect 400, Ergoline GmbH, Blitz, Germany). A ramp protocol of 5 W/min will be used and continued until limiting symptoms, chest pain, signs of ischemia, or arrhythmias develop or other indications for exercise termination appear. Subjects will be instructed to keep pedaling at a constant rate (50–60 rpm) during the test. Subjects will be advised that they will be free to stop whenever they wish but will be encouraged to continue for as long as possible. Respiratory gas exchange measurements will be obtained breath by breath by a commercially available system (Vmax 29C; Sensormedics, Yorba Linda, CA, USA). Peak oxygen uptake (VO_2_max) and respiratory exchange ratio (RER) will be recorded at the mean value of VO_2_ during the last 20 s of the test. The ventilatory anaerobic threshold will be detected by the use of the V-slope method. The ventilation per minute (VE) vs. carbon dioxide production (VCO_2_) relationship (ventilatory efficiency) will be measured by plotting ventilation against VCO_2_ obtained every 10 s of exercise (VE/VCO_2_ slope). The VE/VCO_2_ slope will be calculated as a linear regression function, excluding the non-linear part of the relationship after onset of acidotic drive to ventilation. Peak exercise oxygen pulse will be calculated by dividing derived VO_2_max by the maximum heart rate (HR) during exercise and will be expressed in milliliters per beat. HR will be recorded by ECG at rest, at the anaerobic threshold (AT), and at peak exercise (Guazzi et al., 2018; Pritchard et al., 2021).

There will be a body weight cut-off at 30 Kg based on the need for an appropriate estimation of VO_2_ calculation in children that cannot be reliable for a lower body weight.

#### Echocardiography

An ultrasound system equipped with a 2.5 MHz multifrequency transducer (Aplio, Toshiba, Japan) will be used for complete M-mode, two-dimensional, Doppler, and Tissue Doppler Imaging (TDI) echocardiographic analyses. M-mode and two-dimensional recordings will be made with the patients in the lateral recumbent position. Measures of LV end-diastolic volume (EDV) and end-systolic volume (ESV) will be measured by the modified Simpson's rule. Accordingly, ejection fraction (EF) will be calculated as follows: EF = (EDV – ESV)/ESV^*^100. LV mass will be calculated according to the America Society of Echocardiography-recommended formula: LV mass = 0.8^*^{1.04[(LVIDd + PWTd + SWTd)^3^ – (LVIDd)^3^]} + 0.6 g where PWTd and SWTd are posterior wall thickness at end diastole and septal wall thickness at end diastole, respectively. The following parameters of diastolic function will be measured as the mean of three to five consecutive beats: diastolic transmitral peak velocities, E/A ratio, Isovolumic Relaxation Time (IRT), mitral deceleration time, and pulmonary vein velocities. Quantitative diastolic data will be derived from TDI analysis as elsewhere described.

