**Endpoints:**

The primary endpoint will be a change in *FXN* gene expression level after 12 weeks of treatment. Secondary endpoints will be frataxin protein level, **c**ardiopulmonary exercise test outputs, echocardiographic measures, Nrf2 pathway and mitochondrial biogenesis gene expression, safety, clinical scales, and quality of life scales.

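### The printed ejection-fraction formula divides by end-systolic instead of end-diastolic volume; applied as written, it would misstate EF and distort its change from baseline.

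*Protocol article*

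**What the plan says.** The Echocardiography section (under Clinical measures) first defines the two volumes: "Measures of LV end-diastolic volume (EDV) and end-systolic volume (ESV) will be measured by the modified Simpson's rule". It then fixes the derivation: "ejection fraction (EF) will be calculated as follows: EF = (EDV – ESV)/ESV", with a factor of 100. The denominator is therefore the end-systolic volume. No other section gives a different EF formula or corrects this one.

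Echocardiography is a secondary endpoint. The abstract lists "echocardiographic measures, Nrf2 pathway and mitochondrial biogenesis gene expression, safety, clinical scales, and quality of life scales" among the secondary endpoints, and the Secondary endpoints section again refers to echocardiographic measures as a group. Neither place names EF individually. Table 2 schedules echocardiography at baseline, week 12, week 24 and study interruption. The Statistical analysis section plans a similar repeated-measures approach for the remaining secondary endpoints. Its list of examples does not mention echocardiography, but the general wording would cover it.

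**The concern.** An ejection fraction is the part of the filled (end-diastolic) ventricular volume that is expelled. Dividing the ejected volume by what is left behind gives a different quantity: the ratio of ejected to residual volume. That ratio can exceed 100%, which no fraction of a volume can do, so the formula fails on its own terms.

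The sentence is an operative derivation rule, not background. If it were followed, the EF values entering a between-arm comparison would be on the wrong scale. Because the error is non-linear, the same true change would be recorded as a different number of points depending on where the patient started. With 20 patients planned per arm, a few patients with high EF could then dominate a mean change.

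**Working it through.** **Inputs.** The printed formula and the definitions of EDV and ESV come from the Echocardiography section. The article gives no volumes and no EF distribution, so the EF values below are assumptions chosen to show the range. The article states no EF figure to reproduce.

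**Step 1: what the printed formula computes.** Let f = (EDV − ESV)/EDV be the true EF as a fraction. Then EDV − ESV = f·EDV and ESV = (1 − f)·EDV, so

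(EDV − ESV)/ESV × 100 = 100·f/(1 − f).

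This equals the true EF only when f = 0, that is, when EDV = ESV. It is above the true EF for every f > 0, and above 100% whenever f > 0.5 (ESV less than half of EDV).

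**Step 2: size of the error in a single value** (EDV set to 100 mL for illustration).

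| ESV (mL) | True EF, (EDV − ESV)/EDV × 100 | As printed, (EDV − ESV)/ESV × 100 |
|---|---|---|
| 70 | 30% | 42.9% |
| 60 | 40% | 66.7% |
| 50 | 50% | 100.0% |
| 40 | 60% | 150.0% |
| 35 | 65% | 185.7% |
| 30 | 70% | 233.3% |

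**Step 3: size of the error in a change from baseline.** The same true rise of 5 points is recorded as:

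- 40 to 45%: 81.8 − 66.7 = +15.2 points (before rounding the two values)
- 60 to 65%: 185.7 − 150.0 = +35.7 points
- 65 to 70%: 233.3 − 185.7 = +47.6 points

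**Step 4: what this does to means.** Suppose every patient in both arms truly gains 5 points, but one arm starts at 60% and the other at 65%. The true arm difference in change is 0; the recorded difference is 47.6 − 35.7 = 11.9 points. Likewise, one patient rising from 40 to 45% and another falling from 65 to 60% have a true mean change of 0, but a recorded mean of (15.2 − 35.7)/2, about −10 points.

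**Step 5: can the true value be recovered?** Yes. If r is the printed quantity in percent, then f = r/(100 + r); for example, 150/250 = 0.60. EF can also be recomputed directly from EDV and ESV, which the section says are measured.

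**The case against.** The strongest reply is that this is a one-letter slip in a journal article that condenses a fuller protocol, and that it may never reach the data. Echocardiography is done on a commercial ultrasound system, and the article does not say whether EF is computed there, by hand or in the eCRF. The Electronic case report form section describes no calculated fields, and the list of eCRF data under Good clinical practice does not name echocardiography. All of this stands. It makes the consequence conditional, but it does not make the printed rule correct: the text says that EF will be calculated this way.

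Three stronger readings are tempting, and the article supports none of them.

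- A reader might infer that all EF values in the trial will be wrong. That holds (apart from the trivial EF = 0) only if the formula is applied as printed, which the article does not show.
- A reader might infer that the EF data would be uninterpretable. They would not be lost. The printed quantity increases strictly with true EF, so ranks and the direction of each patient's change survive, and it can be inverted exactly. A value above 100% would also draw attention to the error. What does not survive is the size of changes and any comparison of means.
- Because cardiomyopathy is described as the main cause of death, a reader might infer a safety problem or a misapplied EF threshold. The article contains no EF cut-off. Cardiac eligibility in Table 1 rests on the investigator's judgement, and the specific laboratory withdrawal criteria concern lymphocytes, neutrophils, AST and ALT.

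**Conclusion.** The formula is wrong as written and is corrected nowhere else in the article. That conclusion needs no outside figure. The sizes shown under the working assume that the formula is applied literally, and they use illustrative EF values because the article gives none.

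The reach is narrow. EF is one output among several in the Echocardiography section. LV volumes, LV mass and the diastolic measures do not pass through this formula, and neither do the primary endpoint (FXN expression), the sample size calculation or the main analysis. No trial decision described in the article depends on a computed EF. This is a should-fix error in one component of a secondary endpoint. It does not threaten the trial's main conclusion.

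**What to change.** Replace the denominator, so that the formula reads EF = (EDV − ESV)/EDV × 100. Make the same correction in the full protocol and any analysis specification if the error appears there too. Confirm that the echocardiography software, or any eCRF or analysis derivation, uses the corrected formula. If any EF value was derived with the printed formula, recompute it from the recorded EDV and ESV before EF is analysed or reported.

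The cost is a one-letter correction and a check of the derivation. No new measurements are needed, and the design and sample size do not change.
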